## 9.0 DATA REPORTING/REGULATORY CONSIDERATIONS

### 9.1 Data Management

The principal investigator and research coordinator will be responsible for the database records of patient data. The data will be kept on the research coordinator's computer under password protection. A chart with all the relevant research patient information will be maintained for each patient by the research coordinator.

### 9.2 Confidentiality

Study data will be maintained in password protected computer files. Only research personnel will have access to this information. When possible, identifiers will be removed. Only research personnel and investigators will keep the study data along with identifiers together in the same database under password protection accessible.

## 10. STATISTICAL CONSIDERATIONS

### 10.1 Study Endpoints

#### 10.1.1 Sample Size and Power Consideration

This is a single arm, phase II prospective study to evaluate Soylent™ oral nutritional supplementation for compliance rate and potential impact on therapeutic G-tube rate, nutrition, quality of life, and clinical outcomes with its use during and immediately following chemoradiation in the definitive or adjuvant setting for head and neck cancer. The primary endpoints are compliance rate of Soylent™ oral nutrition supplementation and therapeutic G-tube rate. We plan to enroll 60 patients.

One primary endpoint is to ensure compliance with Soylent™ nutritional supplementation in patients undergoing concurrent chemoradiation. For feasibility in using this supplement for head and neck cancer patients, a goal of more than 50% of patients should continue to use this supplement (to at least 50% of recommended quantities) throughout treatment once initiated.

A therapeutic G-tube placement rate 33% lower than institutional historical control data is the second primary endpoint for this study. Our historical control data notes a 32% G-tube rate for chemoradiation patients, so the goal endpoint is 20%. If, conversely, a 25% higher rate of therapeutic G-tube placement occurs (equating to a 40% G-tube placement rate), this should trigger study stoppage. A sample size of 60 patients achieves 80% power to detect a 33% reduction in G-tube placement rate when comparing to historical control patients (i.e. 20% vs 32%), using a one-sided one-sample exact Binomial test, at a 0.10 significance level.

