## **STATISTICAL METHODS:**

### **SAMPLE SIZE JUSTIFICATION:**

Phase II: This study is designed to examine compliance and efficacy. That is, whether patients who require oral supplementation with Soylent™ continue using the supplement during treatment as directed ( $\geq 50\%$  of the time), and whether therapeutic G-tube rates are reduced by 33% with the utilization of oral nutritional supplementation with Soylent™ compared to our modern cohort of institutional historical control patients (treated from 2015-2016) who had received chemoradiation for head and neck cancer with standard nutritional counseling at our institution. One primary endpoint is to ensure compliance with Soylent™ nutritional supplementation during concurrent chemoradiation. For feasibility of using this meal replacement, we set a goal of more than 50% of patients should continue 50% of recommended daily Soylent intake. A therapeutic G-tube placement rate 33% lower than institutional historical control data is the second primary endpoint for this study. Our historical control data notes a 32% G-tube rate for chemoradiation patients, and we hypothesize reduction in g-tube placement to 20% of our patient population. If, conversely, a 25% higher rate of therapeutic G-tube placement occurs (equating to a 40% G-tube placement rate), study stoppage at an interim analysis period following treatment of 30 patients will be triggered. A sample size of 60 patients achieves 80% power to detect a 33% reduction in G-tube placement rate when comparing to historical control patients (i.e. 20% vs 32%), using a one-sided one-sample exact Binomial test, at a 0.10 significance level.

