## **10.2 Planned Methods of Analysis**

### **10.2.1. Analysis of Primary Endpoints**

For the analysis of compliance, we will calculate the compliance rate and the corresponding 95% exact confidence interval. The G-tube placement rate will be analyzed using one-sample exact Binomial test. The 95% exact confidence interval (CI) will be provided.

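### The 80% power is stated for a 33% reduction in G-tube rate but belongs to 32% versus 20%, a 37.5% reduction; for a 33% reduction it is about 70%

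*Protocol*

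**What the plan says.** Section 10.1.1 defines the second of two primary endpoints in relative terms: "A therapeutic G-tube placement rate 33% lower than institutional historical control data is the second primary endpoint for this study". It then moves to an absolute target: "Our historical control data notes a 32% G-tube rate for chemoradiation patients, so the goal endpoint is 20"%. The power statement joins the two, saying that a sample of 60 "achieves 80% power to detect a 33% reduction in G-tube placement rate when comparing to historical control patients (i.e. 20% vs 32"%), with a one-sided one-sample exact binomial test at the 0.10 level.

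The sample size justification in the synopsis repeats the 33% figure and the power statement. It gives the absolute target as a hypothesis: "we hypothesize reduction in g-tube placement to 20% of our patient population".

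Section 10.2.1 names the one-sample exact binomial test as the analysis of the G-tube rate. The protocol gives no critical count.

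**The concern.** The power sentence presents 33% and 20% versus 32% as the same effect, and section 10.1.1 derives the 20% goal from the 32% control rate as if it followed from a 33% reduction. It does not. Loose rounding is not the obvious explanation, because the companion figure in the same paragraph is exact: a rate 25% higher is equated with 40%, and 0.40/0.32 = 1.25.

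The stake is a stated design property of a primary endpoint. A reader who takes the sentence at its word believes that the chance of missing a true 33% reduction is 20%. If the power belongs to the larger effect, that chance is higher. The mislabelled effect is also the one used to define the endpoint, so it is likely to be carried into reports of the trial.

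**Working it through.** **Inputs, all from section 10.1.1**

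- Patients: n = 60.
- Null (historical) rate: p0 = 0.32.
- Alternative in absolute terms: p1 = 0.20.
- Alternative in relative terms: 33% lower than p0.
- Test: one-sample exact binomial, one-sided, alpha 0.10.
- Stated power: 80%.

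**Step 1. Compare the two descriptions of the effect.**

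- Relative reduction from 32% to 20%: (0.32 − 0.20)/0.32 = 0.375, or 37.5%.
- Rate after a 33% reduction: 0.32 × 0.67 = 0.2144. Reading 33% as one third: 0.32 × 2/3 = 0.2133.

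**Step 2. Find the rejection region.** The test rejects at the largest count c for which P(X ≤ c | 60, 0.32) ≤ 0.10.

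- P(X ≤ 14 | 60, 0.32) = 0.0943.
- P(X ≤ 15 | 60, 0.32) = 0.1526.

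So c = 14, and the attained one-sided alpha is 0.094.

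**Step 3. Reproduce the protocol's figure.** Power at 20% is P(X ≤ 14 | 60, 0.20) = 0.7935. The one-sided normal approximation without continuity correction gives 0.797. Both agree with the stated 80% to within a point. With one-sided 0.05 or two-sided 0.10 the cut-off would be 12, and exact power at 20% would be 0.576. The protocol's 80% was therefore evidently obtained with its stated test at 20% versus 32%.

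**Step 4. Apply the same test to the effect as worded.**

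| True rate | Relative reduction | Power, P(X ≤ 14) |
|---|---|---|
| 20% | 37.5% | 79.3% |
| 21.33% | one third | 71.1% |
| 21.44% | 33% | 70.4% |

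For a true 33% reduction the type II error is 1 − 0.711 = 0.289 to 1 − 0.704 = 0.296, against the 0.20 implied by the power statement.

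**Step 5. Size of the gap in patients, for scale only.** With the same test and a 33% reduction, the smallest n that reaches 80% power is 81. Exact power is saw-toothed, and it stays at or above 80% for every n from 92 up to 159, the largest checked.

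**The case against.** The best defence is that the power sentence spells out its own effect in absolute rates, "when comparing to historical control patients (i.e. 20% vs 32"%), and that for those rates the claim is right. Sample size, test, alpha and absolute rates agree with one another. This stands: the calculation is correct and carries a wrong relative label. It does not remove the point, because the wrong label appears in the synopsis as well as in section 10.1.1 and is also the wording of the endpoint.

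Three stronger readings are tempting, and the protocol supports none of them.

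- *The 20% goal conflicts with the test's cut-off of 14/60 = 23.3%.* It does not. In any test with power well above 50%, the design alternative lies beyond the critical value.
- *The protocol sets two success criteria, and power at a true 20% falls to 57.6% if the observed rate must be 20% or lower (12 of 60 or fewer).* No section states such a rule. The only decision rule specified is the exact binomial test, and the synopsis words 20% as a hypothesis. The fair remark is narrower: calling 20% a goal and 33% lower an endpoint is loose enough that someone could later read an observed-rate criterion into it.
- *The 95% interval contradicts the test, because its upper limit is 32.3%, 34.2% and 36.0% at 12, 13 and 14 of 60, where the test rejects.* Section 10.2.1 says only "The 95% exact confidence interval (CI) will be provided". No decision is attached to the interval, and a two-sided 95% interval need not agree with a one-sided 0.10 test.

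**Conclusion.** The point holds as an error in a stated design property. The 80% power belongs to a 37.5% relative reduction (32% to 20%), where exact power is 79.3%. For the 33% reduction that the protocol names, it is 70.4% to 71.1%, which is 8 to 9 percentage points lower.

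This assumes that 60 patients are analysed, that 32% is treated as a fixed null rate, and that the trial is a single-stage test, as in the protocol's own calculation. The planned interim look with stopping for a high G-tube rate is ignored; such stopping could only lower the power.

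A reader might infer that the trial is too small. The protocol does not support that: for its own absolute rates the sample size delivers the power claimed. Whether 20% or about 21.3% was the intended target cannot be settled from the text.

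**What to change.** In the synopsis and in section 10.1.1, state one alternative with its own power. For example: *60 patients give 79% power to detect a 37.5% relative reduction (32% to 20%) with a one-sided exact binomial test at 0.10 (attained alpha 0.094); power for a 33% reduction, to about 21.3%, is about 70%.* Replace 33% by 37.5% wherever it stands for the change from 32% to 20%, including the sentence that defines the second primary endpoint.

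Describe 20% as the design alternative, and say that success is judged by the exact test, so that neither 20% nor the relative reduction is read as a separate requirement on the observed rate. If a critical count is printed, say that 14 or fewer applies only when exactly 60 patients are analysed. Section 10.5 allows withdrawal and removal, and with another denominator the count must be recalculated from the same test.

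The change is one of wording. It needs no extra patients and leaves the test and alpha as they are. Its only cost is a less favourable stated power for a 33% reduction. If the investigators instead want 80% power for a 33% reduction, the sample size has to be reopened, starting from 81.

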## **10.2 Planned Methods of Analysis**

### **10.2.1. Analysis of Primary Endpoints**

For the analysis of compliance, we will calculate the compliance rate and the corresponding 95% exact confidence interval. The G-tube placement rate will be analyzed using one-sample exact Binomial test. The 95% exact confidence interval (CI) will be provided.

### **10.2.2. Analysis of Secondary Endpoints**

Weight loss and body mass index (BMI) will be collected at each visit and summary descriptive statistics will be calculated at each time points. Repeated measure ANOVA will be used to explore if there are any change in these parameters over time. Treatment breaks will be recorded in days per study patient and summarized. G-tube placement timing will be recorded for patients receiving G-tubes, and the duration of G-tube dependence will be recorded in days per study patient and summarized.

Serum HPV DNA, pre-albumin, albumin, C-reactive protein (CRP), interleukin-6 (IL-6), tumor necrosis factor (TNF), Vitamin A, Vitamin C, Vitamin D, tryptophan, kynurenine, leptin, and adiponectin, complete metabolic panel, and complete blood count and radiosensitivity biomarker panel will be summarized by descriptive statistics by visit time points, and these statistics will be plotted graphically.

Patient-reported QOL according to the University of Washington (UW-QOL) and Functional Assessment of Cancer Therapy-Head & Neck (FACT-HN) questionnaires will be summarized by descriptive statistics by visit time points.

The Kaplan-Meier method will be used to estimate time-to-event endpoints such as local/locoregional control, distant metastasis-free survival and overall survival. Summaries of the number and percentage of patients who have metastasized cancer/died, are still in survival follow-up, are lost to follow-up and have withdrawn consent will be provided along with median distant metastasis-free survival/overall survival.

As exploratory analyses, we will compare these secondary outcome measurements from our study with the control group or previously conducted studies available in the literature to evaluate the potential benefits of adding Soylent™ oral nutrition meal replacement in patients with head & neck cancer undergoing definitive or adjuvant chemoradiotherapy.

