### **1.2 Secondary objectives**

- 1.2.1 To determine weight loss and body mass index (BMI) changes during and following treatment
- 1.2.2 To determine the change in nutritional and metabolic biomarkers during and following treatment
- 1.2.3 To determine physician-reported acute and late toxicities during and following treatment
- 1.2.4 To determine patient-reported quality of life during and following treatment
- 1.2.5 To determine clinical outcomes from treatment

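### Repeated-measures ANOVA for weight and BMI, and Kaplan-Meier for locoregional control, are weak choices where missed weights and deaths are foreseeable (minor)

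*Protocol*

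**What the plan says.** Section 10.2.2 of the Protocol plans descriptive statistics for weight and BMI at each time point, and then one inferential method: "Repeated measure ANOVA will be used to explore if there are any change in these parameters over time". No other model is named for secondary objective 1.2.1 (change in weight and BMI during and after treatment).

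Weights are taken weekly during chemoradiation (section 5.4), which runs for 30 to 35 weekday sessions (section 5.1). They are then taken at follow-up visits at about 1, 3, 6, 12, 16, 18 and 24 months (section 5.5 and the section 8.0 calendar). Section 5.5 allows telemedicine follow-up. Section 10.5 allows withdrawal, including of patients who do not tolerate the meal replacement, and removal of patients who fail the swallow evaluations.

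For disease control, section 10.2.2 says: "The Kaplan-Meier method will be used to estimate time-to-event endpoints such as local/locoregional control". Distant metastasis-free survival and overall survival follow in the same sentence. The event for local/locoregional control is not defined there. Section 5.5 has deaths and their causes recorded.

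**The concern.** Both methods are named in the text, so this is more than detail left for later.

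Classical repeated-measures ANOVA needs a complete, balanced set of values per patient and assumes sphericity. Sphericity is doubtful when the intervals run from one week to several months. A patient who misses one weight drops out of the analysis with all the weights that were observed. Some routes out of the study in section 10.5 (not tolerating the replacement, failing the swallow tests) are plausibly linked to poor intake. Complete patients may therefore differ in weight loss from the rest.

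For local/locoregional control, the protocol lists control separately from the two survival endpoints. The ordinary reading is that death without recurrence is not a failure, and Kaplan-Meier then censors it. Patients who have died are treated as if they could still recur, so one minus the estimate exceeds the proportion who actually fail.

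Section 10.2.2 also plans exploratory comparisons of secondary outcomes with the control group or the literature, so any bias would carry into those.

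**Working it through.** **The nearby stated figure.** The secondary analyses state no number to reproduce. The only computable figure in section 10 is the primary power: "A sample size of 60 patients achieves 80% power to detect a 33% reduction in G-tube placement rate", for 20% against 32%, "using a one-sided one-sample exact Binomial test, at a 0.10 significance level". With 60 patients, rejecting at 14 or fewer tubes gives an exact type I error of 0.0943 and power of 0.793. Rejecting at 15 or fewer would give 0.153, above 0.10. The stated 80% is reproduced to within one point, and nothing below affects it.

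**Number of weights.** 30 to 35 sessions at five per week give 6 to 7 weekly weights. Seven follow-up visits bring the total to 13 to 14 post-baseline weights.

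**Complete cases.** The missing proportion per visit, m, is an assumption, because the protocol gives none. With independent misses over k weights, the complete share is (1 − m)^k. At the other extreme, if the same patients miss every visit, the share is 1 − m. Out of 60 patients:

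| m | k = 13, independent | k = 14, independent | fully clustered |
|---|---|---|---|
| 2% | 0.98^13 = 0.769, 46 | 0.98^14 = 0.754, 45 | 0.98, 59 |
| 5% | 0.95^13 = 0.513, 31 | 0.95^14 = 0.488, 29 | 0.95, 57 |
| 10% | 0.90^13 = 0.254, 15 | 0.90^14 = 0.229, 14 | 0.90, 54 |

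The truth should lie between the independent and clustered columns: death and dropout cluster within patients, while scattered missed weighings do not. If the screening and pre-treatment weights must also be present (15 to 16 values), the independent figures are about 43 to 44 patients at 2%, 26 to 28 at 5% and 11 to 12 at 10%. All of these assume one model over the whole schedule.

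**Locoregional failure at 24 months.** Assume constant cause-specific hazards h1 (failure) and h2 (death without failure). Then 1 − KM = 1 − exp(−2·h1), and cumulative incidence = h1/(h1 + h2) × [1 − exp(−2(h1 + h2))]. All rates are assumed.

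- Fixing 1 − KM, with death probabilities on the same net scale:
  - 10% failure, 5% death: cumulative incidence 9.8%, excess 0.2 points.
  - 15% and 10%: 14.3%, excess 0.7.
  - 20% and 15%: 18.5%, excess 1.5.
  - 20% and 25%: 0.2231/(0.2231 + 0.2877) × (1 − 0.80 × 0.75) = 17.5%, excess 2.5.
- Fixing the true cumulative incidence of failure at 20%:
  - 15% dying first: total hazard −ln(0.65) = 0.431. The failure share is 0.20/0.35 of that, or 0.246, so 1 − KM = 21.8%, excess 1.8.
  - 25% dying first: −ln(0.55) = 0.598. The failure share is 0.20/0.45, or 0.266, so 1 − KM = 23.3%, excess 3.3.

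For scale, the standard error of a 20% proportion in 60 patients is √(0.2 × 0.8/60) = 0.052, a 95% half-width of about 10 points.

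**The case against.** The protocol does not say that patients with a missed weight are dropped, that death is censored for locoregional control, or which visits enter the ANOVA. Those are properties of the named methods as ordinarily applied, and a statistical analysis plan that is not at hand may settle them. The ANOVA is labelled exploratory. The per-visit summaries can use every observed weight, so the description of weight over time does not rest on complete cases alone. Section 10.2.2 also commits to reporting numbers dead, lost to follow-up and withdrawn. Independent misses overstate the loss of complete cases, and the Kaplan-Meier excess is small against sampling error.

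All of that stands. It limits the point to two named methods, stated conditionally. It does not remove the point, because neither named method is the best suited to these data and better ones use the same data.

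A reader might go further in two directions that the text does not support:

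- Tube duration: the protocol says "the duration of G-tube dependence will be recorded in days per study patient and summarized". It is silent on tubes still in place at death or last contact, but silence is not a rule to treat those durations as finished, and censoring rules commonly sit in an analysis plan.
- Biomarkers and quality of life: the objective reads "To determine the change in nutritional and metabolic biomarkers during and following treatment", while the analysis is descriptive by visit. Such summaries do not preclude paired change, so asking for it is a preference for an added analysis and does not correct an error.

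**Conclusion.** The point holds as a minor one. Repeated-measures ANOVA is a poor choice for 13 to 14 post-baseline weights with foreseeable gaps. Under independent misses over 14 weights, its classical form would keep about 29 of 60 patients at 5% missing per visit and 14 of 60 at 10%. Clustering would raise those towards 57 and 54. If death is censored, Kaplan-Meier overstates locoregional failure by about 0.2 to 3 points. Every missingness, failure and death rate here is assumed.

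A reader might infer that the weight trajectory will rest on the healthiest patients and understate loss. The documents do not show this: the direction depends on whether dropout is related to weight loss, and telemedicine visits need not select sicker patients. No primary endpoint, power figure or stopping trigger depends on these analyses.

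**What to change.** In section 10.2.2:

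- Replace repeated-measures ANOVA with a linear mixed model on all observed weights and BMI values, with baseline and each visit as levels of a categorical time factor. Use a parsimonious covariance, such as a spatial structure suited to uneven intervals, or random effects. An unstructured matrix for baseline plus 14 visits would have 15 × 16/2 = 120 parameters, which is heavy for 60 patients. The model relies on missingness being explained by the observed weights, which is weaker than what a complete-case analysis needs but is still an assumption.
- Keep the per-visit descriptive summaries, with the number weighed at each visit.
- Estimate locoregional failure by cumulative incidence with death without recurrence as a competing event. Keep Kaplan-Meier for overall survival and distant metastasis-free survival.

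The cost is analysis wording and programming. The data already planned suffice, since deaths and causes are recorded. No visits or patients are added.

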**SECONDARY OBJECTIVE (S):**

- (1) To determine weight loss and body mass index (BMI) changes during and following treatment
- (2) To determine the change in nutritional and metabolic biomarkers during treatment
- (3) To determine physician-reported acute and late toxicities during and following treatment
- (4) To determine patient-reported quality of life during and following treatment
- (5) To determine clinical outcomes from treatment

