**DURATION OF INTERVENTION AND EVALUATION:**

Nutritional supplementation will take place if weight loss exceeds 5% from the baseline weight taken at study enrollment during concurrent chemoradiation. This is expected to occur in approximately 90% of patients undergoing chemoradiation from our institutional historical control data. Nutritional supplementation may continue until the month following completion of chemoradiation (up to approximately 3 month's total). Patients will be evaluated weekly by the study site's clinical dietitian and clinical staff to assess weight changes as is done for all patients undergoing chemoradiation to the head and neck. Patients will remove their shoes, items from their pockets, and any coats or sweaters. The dietitian and study staff will also determine the amount of supplementation utilized and assess the need of a G-tube during chemoradiation. G-tube placement will be recommended if a patient reaches 10% weight loss and/or is not meeting nutritional requirements as assessed by a dietitian. Patients will be required to be in a swallow preservation program with the Speech Pathology Clinic for minimizing dysphagia and aspiration surveillance. Clinical nutritional follow-up will continue as long as the patient is recommended to have nutritional supplementation. Weight measurements will be routinely taken at every follow-up visit. Blood/cheek swab sample collection (whenever feasible) for future analysis may occur at baseline (prior to treatment), at the conclusion of treatment (last week of chemoradiation), and at the 3-month follow-up visit. The University of Washington Quality of Life (UW-QOL) and Functional Assessment of Cancer Therapy Head & Neck (FACT-HN) questionnaires will be used

to assess QOL prior to beginning chemoradiation and at every routine follow-up after completing chemoradiation. Routine clinical follow-up will last for a minimum of 2 years.

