### **5.5 Patient Follow-Up after Treatment**

Patients will be followed clinically after treatment per standard of care, including routine evaluation of patient-reported QOL metrics (UW-QOL and FACT-HN questionnaires), physician-reported acute and late toxicities, body weight, and clinical/radiographic evaluations for local/locoregional recurrence, and distant metastases. A patient death, and its cause, will be recorded by the treating radiation oncologist in the study records if this occurs. Patients will continue routine follow-up visits in radiation oncology at approximately 1, 3, 6, 12, 16, 18, and 24 months as is routine at our institution for patients with locally advanced head and neck cancer surveillance. When practical and in the best interest of the subject, follow-up visits may occur via telemedicine. The UW-QOL and FACT-HN questionnaires may be administered electronically or by telephone. Serum (50 mls)/cheek swab samples will be taken only at the conclusion of chemoradiation (in the last week of treatment, as noted above) and at the 3-month follow-up visit. The 3-month follow-up visit labs will attempt to be drawn with necessary labs, if needed. Otherwise, this will be a separate blood draw. All serum and cheek swab sampling done for basic science research (i.e., those described in this section) will occur only when feasible

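### Objective 1.2.2 asks for the change in nutritional and metabolic biomarkers, but section 10.2.2 plans only visit-by-visit summaries, which give no valid interval for that change (minor)

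*Protocol*

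**What the plan says.** **The objective.** Section 1.2 of the protocol gives secondary objective 1.2.2 as "To determine the change in nutritional and metabolic biomarkers during and following treatment". The synopsis has a shorter form: "To determine the change in nutritional and metabolic biomarkers during treatment". Both name change as the quantity of interest.

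**The sampling.** Sections 5.3 to 5.5 provide for blood from the same patients at baseline, at the end of chemoradiation (last week) and at the 3-month visit. Section 5.5 adds a condition: "All serum and cheek swab sampling done for basic science research (i.e., those described in this section) will occur only when feasible". The synopsis and the study calendar footnote carry the same caveat.

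**The analysis.** Section 10.2.2 lists the serum markers together with the metabolic panel, the blood count and the radiosensitivity panel, and says that they "will be summarized by descriptive statistics by visit time points, and these statistics will be plotted graphically". It names no change from baseline, paired estimate, confidence interval or longitudinal model for them. One paragraph earlier, after the descriptive statistics for weight loss and BMI, the section adds: "Repeated measure ANOVA will be used to explore if there are any change in these parameters over time". In that sentence the parameters are weight loss and BMI only.

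**The concern.** The protocol names change as its target and collects the serial samples needed to measure it. It then states an analysis that describes each visit separately. A reader of the resulting tables can subtract one visit mean from another. The only standard error that can be built from the two published spreads, however, is the one for independent groups, which ignores that the same patients contribute to both.

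The second issue is composition. If research blood "will occur only when feasible", the patients in the later summaries may be a subset of those in the baseline summary. Patients who are doing badly may be harder to sample. Part of an apparent rise or fall could then come from who gave blood.

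At stake is the interpretation of one secondary objective, not a trial decision.

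**Working it through.** **Inputs from the protocol.** N = 60 (section 10.1.1); three planned draws per patient (sections 5.3 to 5.5); sampling conditional on feasibility (section 5.5). The protocol gives no design figure for the biomarkers. Its only power figure concerns the G-tube endpoint (80%, 20% against 32%, one-sided exact binomial test at 0.10). That figure reproduces: rejecting at 14 or fewer G-tubes in 60 gives an exact level of 0.0943 and power of 0.7935. It does not depend on the biomarker analysis.

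**Assumptions, because the protocol gives none.** Equal SD at both visits, with results in SD units; within-patient correlation r of 0.3, 0.5 or 0.7; n1 = 60 baseline samples; n2 = 40 to 60 later samples, all from patients with a baseline sample.

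**Step 1: complete data, n1 = n2 = 60.**
- Visits read as independent: SE = √(2/60) = 0.183.
- Within-patient change: SE = √(2(1−r)/60) = 0.153, 0.129 and 0.100 for r = 0.3, 0.5 and 0.7.
- Ratio: 1/√(1−r) = 1.20, 1.41 and 1.83.
- 95% half-width (1.96 × SE): 0.36 SD, against 0.30, 0.25 and 0.20 SD.

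The difference of visit means here equals the mean within-patient change. The point estimate is right, and only its uncertainty is unavailable or misread.

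**Step 2: the real loss of precision when later samples are missing.** The true sampling error of the difference of visit means already benefits from the overlap of patients.
- Difference of visit means: SE = √(1/60 + 1/n2 − 2r/60).
- Likelihood-based repeated-measures model: SE = √((1−r²)/n2 + (1−r)²/60).

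| n2 | r | Visit-mean difference | Mixed model | Ratio |
|---|---|---|---|---|
| 60 | 0.3 / 0.5 / 0.7 | 0.153 / 0.129 / 0.100 | 0.153 / 0.129 / 0.100 | 1.00 / 1.00 / 1.00 |
| 50 | 0.3 / 0.5 / 0.7 | 0.163 / 0.141 / 0.115 | 0.162 / 0.138 / 0.108 | 1.01 / 1.02 / 1.07 |
| 40 | 0.3 / 0.5 / 0.7 | 0.178 / 0.158 / 0.135 | 0.176 / 0.151 / 0.119 | 1.01 / 1.04 / 1.13 |

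The visit-mean difference is thus 0 to 13% less precise than the model estimate.

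**Step 3: composition.** Assume no true change, two-thirds of patients resampled, and odds of resampling that double per SD of better baseline value. Integrating over a standard normal baseline, the resampled patients have a mean baseline of +0.21 SD.
- Their expected later mean is r × 0.21, while the baseline mean over all patients is 0. The visit-mean difference is therefore 0.3 × 0.21 = +0.06, 0.5 × 0.21 = +0.11 (0.105 before rounding) and 0.7 × 0.21 = +0.15 SD.
- The raw mean change among complete pairs is (r−1) × 0.21 = −0.15, −0.11 and −0.06 SD. It errs in the opposite direction.
- An estimate that conditions on each patient's baseline gives 0.00.

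The third line is why a model using all available samples is preferable to simple paired differences.

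**The case against.** **No test between visits is planned.** The protocol does not itself treat the visits as independent groups. A reader might turn the Step 1 ratio into a loss of power, but no such test exists in the plan. The ratio describes how the tables could be misread, not a planned analysis. This part of the objection stands.

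**The visit-mean difference is not materially imprecise.** This also stands: Step 2 shows a small loss. What is missing is a valid interval.

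**Descriptive summaries could include change, and the detail belongs in an analysis plan.** This stands in part. The wording does not forbid change scores, and with complete samples the point estimate can be recovered. But the protocol did choose to state a method here. That method does not address the objective's own quantity, while weight and BMI in the same section receive a longitudinal one.

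**The selective sampling is hypothetical.** True. The protocol gives no missingness rate or mechanism. At r = 0.5 the shift of about 0.11 SD is below one standard error of the visit-mean difference (0.158 with 40 resampled). The caveat also covers only research sampling; section 5.2 has chemistries and blood counts taken routinely during chemotherapy, so not every listed marker need be affected.

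**Quality of life.** A reader might extend the point to the questionnaires, which "questionnaires will be summarized by descriptive statistics by visit time points". The documents do not support this well. Objective 1.2.4 does not name change, the study calendar marks no questionnaire at 12 or 24 months, and a mixed model would not resolve the absence of scores after death.

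**Nothing decisive depends on it.** Correct. The arm is uncontrolled, no biomarker threshold is set, and a change during chemoradiation could not be attributed to the supplement under any model. This limits the severity.

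**Conclusion.** The point holds, as a minor one. The stated biomarker analysis does not match objective 1.2.2, because it yields no valid standard error or interval for the change. Reading the visits as independent would overstate the standard error 1.2 to 1.8 times with complete data, for r of 0.3 to 0.7. If sampling is selective in the way assumed, the visit-mean difference could shift by about +0.06 to +0.15 SD with no true change. Both ranges rest on assumed correlations, and the second also on an assumed sampling pattern.

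A reader might infer that the objective is not estimated at all. That goes too far: with complete data the visit-mean difference is the mean within-patient change, and the efficiency loss against a mixed model is 0 to 13% for 40 to 60 of 60 patients resampled. The primary endpoints and the sample size are unaffected.

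**What to change.** In section 10.2.2, for the serum nutritional and metabolic biomarkers:

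- Estimate the change from baseline to the last week of chemoradiation and to 3 months, each with a 95% confidence interval. Use a linear mixed model with visit as a categorical factor and a within-patient covariance, fitted to all available samples. Use the log scale for skewed markers such as CRP and IL-6.
- Report, per time point, the number of patients with both a baseline and a later sample.
- Keep the by-visit tables and plots as supportive description.
- Report the germ-line radiosensitivity panel once, not by visit, since it does not change over time.

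The cost is a few lines of wording and modest programming on data already being collected, with no new samples, visits or patients. The downsides are slightly more output and reliance on later samples being missing at random given the observed values.
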